### List of study efficacy endpoints

Primary efficacy endpoints

Change from baseline in HbA_1c_ after 52 and 104 weeks of treatment

Key secondary endpoints

Change from baseline in body weight after 52 and 104 weeks of treatment

Occurrence of confirmed hypoglycemic AEs^†^ during 52 and 104 weeks of treatment

Change from baseline in SBP and DBP after 52 and 104 weeks of treatment

Exploratory endpoints

^†^Blood glucose ≤70 mg/dL and/or assistance required.

^‡^Calculated as slope of least-squares regression line including all measurements from week 28 to last available measurement.

*Legend*: *HbA*_*1c*_ glycosylated hemoglobin, *AEs* adverse events, *SBP* systolic blood pressure, *DBP* diastolic blood pressure, *FPG* fasting plasma glucose, *MDG* mean daily glucose, *PPG* post-prandial glucose, *MTT* meal tolerance test, *DXA* Dual Energy X-ray Absorptiometry, *VAT* visceral adipose tissue, *SAT* subcutaneous adipose tissue, *MRI* magnetic resonance imaging, *BP*: blood pressure.

*Glucose control*

HbA_1c_ <7.0% or <6.5% after 52, 104 and 208 weeks of treatment

HbA_1c_ lowering by ≥0.5% after 52, 104 and 208 weeks of treatment

Change from baseline in HbA_1c_ after 208 weeks of treatment

Coefficient of durability for HbA_1c_ response^‡^

Change from baseline in FPG after 52, 104 and 208 weeks of treatment

Change from baseline in MDG (8-point) after 52, 104 and 208 weeks of treatment (sub-study)

Change from baseline in 2-h PPG after 52, 104 and 208 weeks of treatment and follow-up (4 weeks after treatment discontinuation) (sub-study)

Biomarkers of insulin secretion and resistance after 104 and 208 weeks of treatment and (in the MTT sub-study) follow-up (4 weeks after treatment discontinuation)

Confirmed hypoglycemic AEs^†^ during 208 weeks of treatment

*Weight loss*

Change from baseline in body weight of >2% and >5% after 52, 104 and 208 weeks of treatment

Change from baseline in body weight after 208 weeks of treatment and follow-up (4 weeks after treatment discontinuation)

Change from baseline in waist circumference after 52, 104 and 208 weeks of treatment and follow-up (4 weeks after treatment discontinuation)

Changes from baseline in trunk fat, limb fat, fat-free mass and total fat mass (using DXA scan) after 52, 104 and 208 weeks of treatment (sub-study)

Changes from baseline in bone mineral density and T-scores (using DXA scan) after 52, 104 and 208 weeks of treatment (sub-study)

Changes from baseline in abdominal VAT, abdominal SAT and VAT/SAT ratio (using MRI) after 52, 104 and 208 weeks of treatment (sub-study)

*Blood pressure*

Proportion of patients with BP <130/80 mmHg after 52, 104 and 208 weeks of treatment

Change from baseline in SBP and DBP after 208 weeks of treatment and follow-up (4 weeks after treatment discontinuation)

*Composite endpoints*

HbA_1c_ <7.0% or HbA_1c_ reduction ≥1.0%, no confirmed hypoglycemic AEs, and weight loss >2% after 52, 104 and 208 weeks of treatment

HbA_1c_ <6.5% or HbA_1c_ reduction ≥1.0%, no confirmed hypoglycemic AEs, and weight loss >2% after 52, 104 and 208 weeks of treatment

*Lipid profile*

Change from baseline in lipid profile after 52, 104 and 208 weeks of treatment and follow-up (4 weeks after treatment discontinuation)

Change from baseline in body weight will be evaluated as a key secondary endpoint. Exploratory endpoints include the proportion of patients with >5% reduction in body weight and change in waist circumference. The effects of empagliflozin and SU on body fat content and distribution (e.g. changes in total body fat, trunk fat, abdominal visceral adipose tissue and subcutaneous adipose tissue) will be assessed in a dedicated body composition sub-study using Dual Energy X-ray Absorptiometry (DXA) and Magnetic Resonance Imaging (MRI) scans.

Changes from baseline in systolic and diastolic blood pressure will be evaluated as key secondary endpoints. Exploratory endpoints include the proportion of patients achieving blood pressure control (<130/80 mmHg) and effects on plasma lipids. The effect of treatment on the composite endpoint of HbA_1c_ <7.0% and/or a reduction in HbA_1c_ of ≥1.0%, with no confirmed hypoglycemic events, and weight loss of >2% body weight, will be examined as an exploratory endpoint.

Safety endpoints include all AEs reported during the trial; vital signs; clinical laboratory findings; prospectively adjudicated CV events; markers of renal function/damage including changes from baseline in creatinine, eGFR and albuminuria, as well as the incidence of new-onset albuminuria; laboratory bone markers, and, in the body composition sub-study, changes from baseline in bone mineral density, as determined by DXA scan.

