**Figure 1 F1:**
[figure not shown]
**Study design. ***Glimepiride was initiated at 1 mg/day, with the recommendation to uptitrate if fasting plasma glucose levels (assessed by home monitoring) were >110 mg/dL, to 2 mg/day at week 4, to 3 mg/day at week 8, and to a maximum of 4 mg/day at week 12. Uptitration can be withheld if it would place the patient at risk of hypoglycemia. Glimepiride dose can be downtitrated at any time to prevent recurrent hypoglycemia.

Patients received diet and exercise counseling at the beginning of the placebo run-in period based on local recommendations. Patients will be reminded about the importance of following the recommended diet and exercise plan at every study visit. Rescue therapy can be initiated during the 4-year treatment period if a patient has the following confirmed blood glucose levels after an overnight fast: >240 mg/dL during weeks 1 to 12, >200 mg/dL during weeks 12 to 28 and >180 mg/dL (or HbA1c >8%) after week 28. The choice and dosage of rescue medication are at the discretion of the investigator, but must not include an SU or SGLT2 inhibitor. The use of any anti-diabetes agents other than study medication, stable background metformin IR and rescue therapy is not permitted. There are no additional restrictions on the use of concomitant medications, except for those listed in the exclusion criteria (Table 1), which will be monitored throughout the trial.

The Clinical Trial Protocol was approved by the relevant Institutional Review Boards and local Independent Ethics Committees and the trial was conducted in accordance with the Declaration of Helsinki and the International Conference on Harmonization guidelines for Good Clinical Practice.

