The efficacy analyses will be performed on the full analysis set (FAS), i.e. all randomized patients who received ≥1 dose of study drug and had a baseline HbA_1c_ assessment, using the last observation carried forward (LOCF) methodology for imputation of missing data. Efficacy data after the first intake of rescue medication will be set to missing. For the primary endpoint, an analysis of covariance (ANCOVA) model will be used with randomized treatment, eGFR and geographical region as fixed effects and baseline HbA_1c_ as a covariate. Sensitivity analyses of the primary endpoint will be undertaken in the per-protocol set (PPS104: patients in the FAS without any important protocol violations during the first 104 weeks’ treatment, such as violating the inclusion or exclusion criteria, changing dose of background metformin IR, taking the incorrect trial medication, or compliance <80%), FAS104 completers (patients in the FAS who complete the 2-year treatment period and have HbA_1c_ values for the end of the treatment period) and PPS104 completers (FAS104 completers who do not have any important protocol violations) using the same model and the LOCF approach to missing data. Additional sensitivity analyses include a restricted maximum likelihood-based model repeated measures (MMRM) approach in observed cases in the FAS to determine the effect of empagliflozin on HbA_1c_ over time. Secondary endpoints will be analyzed using the same model as the primary endpoint, with the continuous baseline values of the endpoint being investigated included as an additional covariate. Blood pressure data after changes in antihypertensive medication will be set to missing and imputed using LOCF.

All safety endpoints will be analyzed in the treated set, i.e. all patients who received ≥1 dose of study drug and presented using descriptive statistics. Confirmed hypoglycemic events will be analyzed using Cochran-Mantel Haenszel tests stratified by baseline HbA_1c_ (<8.5% vs. ≥8.5%). Change from baseline in lipid parameters will be analyzed using ANCOVA. Time-to-event analyses (Kaplan-Meier) for onset of new microalbuminuria (albumin/creatinine ratio [ACR] ≥30 mg/g), onset of new macroalbuminuria (ACR ≥300 mg/g), and progression from microalbuminuria to macroalbuminuria groups compared using log-rank tests.

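### Under the set-to-missing and LOCF rule, some patients who started rescue can still count as responders on the exploratory HbA1c-reduction and composite endpoints

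*Protocol article*

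**What the plan says.** The list of study efficacy endpoints contains three kinds of exploratory HbA1c response:

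- absolute targets: HbA1c "<7.0% or <6.5% after 52, 104 and 208 weeks of treatment";
- a relative reduction: HbA1c "lowering by ≥0.5% after 52, 104 and 208 weeks of treatment";
- two composites, in which the HbA1c part is met by a target (below 7.0% or below 6.5%) or by a "reduction ≥1.0%, no confirmed hypoglycemic AEs, and weight loss >2% after 52, 104 and 208 weeks of treatment".

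None of these carries a condition on rescue.

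The rescue text under Figure 1 is permissive: "Rescue therapy can be initiated during the 4-year treatment period". The late trigger is a confirmed fasting glucose ">180 mg/dL (or HbA1c >8%) after week 28".

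The Statistical analysis section then says "Efficacy data after the first intake of rescue medication will be set to missing". It performs the efficacy analyses on the full analysis set "using the last observation carried forward (LOCF) methodology for imputation of missing data". It states no separate rule for binary endpoints. The Discussion adds that patients who take rescue may remain in the trial.

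**The concern.** A responder rate is usually read as the share of patients who did well on the drug they were assigned. After week 28 the protocol accepts HbA1c above 8% as a ground for adding another drug. The reduction endpoints have no ceiling, and screening admits HbA1c up to 10%, so one HbA1c value can both permit rescue and satisfy a reduction. Deleting later data and carrying the last value forward then fixes that value as the result at every later time point. A patient whose assigned treatment was supplemented because control was judged insufficient stays in the success column.

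At stake is how the reduction endpoint and the composites can be read. The composites matter most here, because they look like measures of overall treatment success. The trial also has durability as a stated interest, and a patient who responds, deteriorates and needs rescue is a durability failure.

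**Working it through.** **Plan's own figures.** The article gives no responder rate and no rescue rate to reproduce. Its one design calculation, 698 per arm, does not depend on this point. It is consistent with its inputs: margin 0.3, true difference 0.05, SD 1.2, one-sided 1.25% and 95% power give 696 with the normal formula and 698 with the noncentral t.

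**Step 1: the rules applied to single patients** (rescue on HbA1c above 8% after week 28)

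| Baseline | Last value before rescue | Fall | Above 8%? | Fall ≥0.5? | Fall ≥1.0? |
|---|---|---|---|---|---|
| 9.8 | 8.7 | 1.1 | yes | yes | yes |
| 9.0 | 8.4 | 0.6 | yes | yes | no |
| 8.5 | 8.0 | 0.5 | no | yes | no |

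The first two patients, if rescued, carry 8.7% or 8.4% forward and are scored on it. The third does not meet the HbA1c trigger.

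**Step 2: who can be affected through the HbA1c trigger.** The last pre-rescue value must exceed 8%, and baseline minus that value must reach the required fall.

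- Fall ≥0.5: baseline > 8.0 + 0.5 = 8.5%. Table 4 has 372 of 1545 at 8.5% or above, which is 24.1%.
- Fall ≥1.0: baseline > 8.0 + 1.0 = 9.0%. Table 4 gives no count. A normal distribution with mean 7.92 and SD 0.84 gives P(Z > (9.0 − 7.92)/0.84) = P(Z > 1.286) = 9.9%, about 153 of 1545. The same approximation at 8.5% gives 24.5%, close to the observed 24.1%.
- Targets below 7.0% or 6.5%: a value cannot be below 7.0% and above 8% at once, so the overlap is zero. Only rescue on fasting glucose could coexist with these targets.

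The 24% and 10% are ceilings for the HbA1c trigger only. Rescue on fasting glucose could add patients with a lower baseline, and the document offers nothing to size that.

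**Step 3: meeting the trigger at one visit.** The following are assumptions, not figures from the document: mean change −0.4 to −0.9, SD of change 0.8 to 1.2, slope on baseline 0 to −0.5. About 4–6% of all patients then have a fall of at least 0.5 with HbA1c above 8%, and about 1–2% a fall of at least 1.0 with HbA1c above 8%. These patients meet the criterion; not all of them would be rescued.

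**Step 4: accumulation under LOCF.** HbA1c is measured at weeks 40, 52, 65, 78 and 91 before week 104 (Table 2). Rescue can start after any of these, and the value is frozen from then on. Simulation assumptions: 400,000 patients; mean fall 0.6–0.8; slope on baseline 0–0.5; drift 0.1–0.3 per year; between-patient SD 0.6; visit SD 0.3. Uptake is the chance of starting rescue at each visit with HbA1c above 8%.

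| Time point | Uptake | Rescued and fall ≥0.5 (% of all patients) | Rescued and fall ≥1.0 (% of all patients) |
|---|---|---|---|
| Week 104 | 50–100% | 7–11 | 1.3–3.9 |
| Week 104 | 25% | 4.6–5.9 | 0.8–2.0 |
| Week 104 | 10–25% | about 2–6 | up to about 2 |
| Week 52 | 50–100% | 2.4–6.7 | 0.6–2.2 |

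Week 52 is lower because only the week-40 visit falls between week 28 and week 52. The last column describes one component of the composites. The conditions on weight loss and hypoglycemia would reduce it further, and that reduction was not computed.

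**The case against.** **A relative reduction is a legitimate endpoint.** It measures size of response, while the rescue threshold measures absolute control. A patient at 8.7% after starting at 9.8% has responded and is still above 8%. Absolute control is reported separately through the below 7.0% and below 6.5% targets. This stands: the definitions do not contradict the rescue rule, and the thresholds need no change. The problem lies only in how a value is assigned after rescue.

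**The analysis plan may handle it.** The article condenses a fuller protocol, and a rule for exploratory binary endpoints could sit there. That is possible. But the article does state a rule for the efficacy analyses and makes no exception, so the result follows from what is written and not from an omission.

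**The larger percentages rest on high uptake.** This also stands. In a run that put rescued ≥0.5% responders at 8.6–11.3% of all patients and 27–30% of rescued patients, the implied share rescued by week 104 is roughly 30–40% (8.6/0.27 = 32%; 11.3/0.30 = 38%). Nothing in the document supports or excludes that.

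**Stronger readings that the document does not support.**

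- A reader might infer that rescued patients in general are scored as successes. They are not. Rescue is only permitted, values obtained on rescue are never used, and in the run just cited 70–73% of rescued patients missed the 0.5% reduction.
- A reader might infer that all HbA1c responder endpoints are affected alike. The two absolute targets have no overlap with the HbA1c trigger.
- A reader might infer that the effect hides a durability difference between the drugs. No two-arm calculation was made, and durability has its own endpoint, the coefficient of durability. A differential effect is possible but not shown.

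**Conclusion.** The point holds in limited form. Applied as written, the set-to-missing and LOCF rule counts some rescued patients as responders on the ≥0.5% reduction endpoint and on the ≥1.0% component of both composites. This applies at weeks 52 and 104, and at week 208 if the same rule is used there.

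Through the HbA1c trigger, the patients concerned are those with a baseline above 8.5% (about 24%) or above 9.0% (about 10%, normal approximation) whose last pre-rescue value still meets the reduction. At week 104 the share is roughly 2–11% of all patients for the first rule and roughly 1–4% for the second, and below 1% for the second where uptake is low. The width of these ranges mainly reflects unknown rescue uptake.

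The endpoints are exploratory and outside the Table 3 hierarchy. Primary and key secondary inference, power and sample size are unaffected. Severity: minor.

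**What to change.** Add one sentence to the analysis of the HbA1c responder and composite endpoints: *a patient who started rescue medication before the time point is a non-responder at that time point, and no pre-rescue value is carried forward for these endpoints.* Apply it to the absolute targets as well, so that rescue on fasting glucose is treated in the same way. Leave the response thresholds, the rescue criteria and the continuous HbA1c analysis as they are. Settle the wording before unblinding.

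The cost is small. The date of first rescue intake is already needed to set later data to missing, so nothing new is collected. The downside is that responder rates will fall somewhat in both arms.

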### Statistical analysis

The main analysis will be undertaken after 104 weeks of treatment; an interim analysis is planned after 52 weeks of treatment (Table 3). The non-inferiority of empagliflozin compared to glimepiride on the primary endpoint of change from baseline in HbA_1c_ will be tested after 52 and 104 weeks of treatment based on a one-sided significance level of 1.25%. In total, 698 patients per arm are required to provide a power of ≥95% to show non-inferiority, based on a margin of 0.3%, on the primary endpoint at 52 and 104 weeks at this significance level if the true treatment effect is 0.05% (adjusted for multiplicity related to the 52-week analysis), and the standard deviation is 1.2%.

**Table 3 T3:** Hierarchical statistical methods

	**Analysis**	**Testing hierarchy for 52-week analysis (interim analysis)**	**Testing hierarchy for 104-week analysis (main analysis)**
1	Primary	Non-inferiority in change from baseline in HbA_1c_	Non-inferiority in change from baseline in HbA_1c_
2	Secondary	Superiority in change from baseline in body weight	Superiority in change from baseline in body weight
3		Superiority in incidence of confirmed hypoglycemic AEs	Superiority in incidence of confirmed hypoglycemic AEs
4		Superiority in change from baseline in SBP	Superiority in change from baseline in HbA_1c_
5		Superiority in change from baseline in DBP	Superiority in change from baseline in SBP
6			Superiority in change from baseline in DBP

*Legend*: *HbA*_*1c*_ glycosylated hemoglobin, *AEs* adverse events, *SBP* systolic blood pressure, *DBP* diastolic blood pressure.

The superiority of empagliflozin compared to glimepiride on the primary endpoint will be tested after 104 weeks’ treatment. Other key secondary endpoints will be tested for superiority at weeks 52 and 104, based on a significance level of 2.5% (two-sided) (Table 3). All other exploratory tests, including all analyses conducted at 208 weeks, will be 2-sided at a 5% level (no multiplicity adjustment).

The efficacy analyses will be performed on the full analysis set (FAS), i.e. all randomized patients who received ≥1 dose of study drug and had a baseline HbA_1c_ assessment, using the last observation carried forward (LOCF) methodology for imputation of missing data. Efficacy data after the first intake of rescue medication will be set to missing. For the primary endpoint, an analysis of covariance (ANCOVA) model will be used with randomized treatment, eGFR and geographical region as fixed effects and baseline HbA_1c_ as a covariate. Sensitivity analyses of the primary endpoint will be undertaken in the per-protocol set (PPS104: patients in the FAS without any important protocol violations during the first 104 weeks’ treatment, such as violating the inclusion or exclusion criteria, changing dose of background metformin IR, taking the incorrect trial medication, or compliance <80%), FAS104 completers (patients in the FAS who complete the 2-year treatment period and have HbA_1c_ values for the end of the treatment period) and PPS104 completers (FAS104 completers who do not have any important protocol violations) using the same model and the LOCF approach to missing data. Additional sensitivity analyses include a restricted maximum likelihood-based model repeated measures (MMRM) approach in observed cases in the FAS to determine the effect of empagliflozin on HbA_1c_ over time. Secondary endpoints will be analyzed using the same model as the primary endpoint, with the continuous baseline values of the endpoint being investigated included as an additional covariate. Blood pressure data after changes in antihypertensive medication will be set to missing and imputed using LOCF.

All safety endpoints will be analyzed in the treated set, i.e. all patients who received ≥1 dose of study drug and presented using descriptive statistics. Confirmed hypoglycemic events will be analyzed using Cochran-Mantel Haenszel tests stratified by baseline HbA_1c_ (<8.5% vs. ≥8.5%). Change from baseline in lipid parameters will be analyzed using ANCOVA. Time-to-event analyses (Kaplan-Meier) for onset of new microalbuminuria (albumin/creatinine ratio [ACR] ≥30 mg/g), onset of new macroalbuminuria (ACR ≥300 mg/g), and progression from microalbuminuria to macroalbuminuria groups compared using log-rank tests.

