## Discussion

This head-to-head trial aims to establish comparative effectiveness between the SGLT2 inhibitor empagliflozin and the sulfonylurea glimepiride, used as second-line therapy in patients with T2DM in whom metformin and diet/exercise has failed, with regard to glycemic control, beta-cell function, diabetes-associated comorbidities such as obesity and hypertension, and safety, including macro- and renal microvascular complications, over 4 years.

This study is the largest head-to-head trial comparing an SGLT2 inhibitor with an SU to date [45,46]. As is typical of patients with T2DM, most of the patients in this study were overweight or obese and the majority had hypertension. The large number of patients enrolled in this study will enable important sub-group analyses to be performed, including analyses by the stratification factors baseline HbA_1c,_ eGFR, and region, but also analyses by baseline HOMA-IR, HOMA-B and BMI to characterize the efficacy of empagliflozin versus glimepiride in distinct subpopulations. Every effort is being made to keep patients randomized in the trial, for example, by allowing downtitration of SU to prevent recurrent hypoglycemia, by allowing patients who take rescue medication to stay in the trial, and by imposing very limited restrictions on concomitant medications. Every effort is being made to follow-up with patients who discontinue study drug.

Durability of efficacy and preservation of beta-cell function are important unmet medical needs in the treatment of patients with T2DM. This study will compare the effect of the insulin secretagogue glimepiride with empagliflozin, which has an insulin-independent mode of action, on the annualized slope of glycemic control (coefficient of durability) and biomarkers of insulin secretion over 4 years. Furthermore, the study design includes a 4-week follow-up period to assess, using a mixed MTT, whether empagliflozin truly delays or masks deterioration of beta-cell function during treatment through urinary glucose excretion.

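### Read as written, the LOCF and rescue-deletion rule puts on-drug values into the four-week off-drug endpoints and so shrinks the within-arm change after stopping treatment

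*Protocol article*

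**What the plan says.** The Statistical analysis section of the Protocol article sets one missing-data rule for the efficacy analyses, to be run on the full analysis set: "using the last observation carried forward (LOCF) methodology for imputation of missing data. Efficacy data after the first intake of rescue medication will be set" (that is, such data count as missing). A further rule covers blood pressure: "Blood pressure data after changes in antihypertensive medication will be set to missing and imputed using LOCF". None of these sentences is limited to on-treatment visits.

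The List of study efficacy endpoints contains exploratory endpoints taken after study drug has been stopped. One is "Change from baseline in 2-h PPG after 52, 104 and 208 weeks of treatment and follow-up (4 weeks after treatment discontinuation) (sub-study". For blood pressure the list gives "Change from baseline in SBP and DBP after 208 weeks of treatment and follow-up (4 weeks after treatment discontinuation". For beta-cell markers the entry reads "Biomarkers of insulin secretion and resistance after 104 and 208 weeks of treatment and (in the MTT sub-study) follow-up (4 weeks after treatment discontinuation". Body weight, waist circumference and lipids are also listed at this follow-up.

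The Discussion gives the reason for the visit. A meal test at follow-up is to assess "whether empagliflozin truly delays or masks deterioration of beta-cell function during treatment through urinary glucose excretion".

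**The concern.** A follow-up endpoint of this kind is useful only if it describes the patient off drug. The stated rule can fill it with an on-drug value in three ways:

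- A patient without a follow-up measurement has the last on-treatment value carried across the last dose.
- A rescued patient who does attend has the real off-drug measurement deleted and replaced by a value from before rescue.
- For blood pressure, the same happens after a change in antihypertensive medication.

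In each case the patient is scored as if stopping the drug had changed nothing. What is at stake is the on-to-off contrast, which the Discussion presents as a design feature for separating preserved beta-cell function from a decline hidden by urinary glucose loss.

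**Working it through.** **The plan's own figure.** The only design calculation is the non-inferiority sample size: margin 0.3%, true difference 0.05%, SD 1.2%, one-sided 1.25%, power 95%. n = 2 × 1.2² × (2.2414 + 1.6449)² / 0.25² = 696 per arm by the normal approximation, and 698 with the noncentral t distribution. The stated 698 is reproduced. It does not bear on this point.

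**Coverage.** The rule applies to efficacy analyses without restriction, and the follow-up endpoints stand in the efficacy list. On plain wording the rule covers 2-h PPG, meal-test biomarkers, body weight, waist and SBP/DBP at follow-up. Lipids are uncertain: they are in the efficacy list, but their ANCOVA is described in the safety paragraph.

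**Who could be affected.**
- Study design allows rescue throughout the four years, and the Discussion says rescued patients stay in the trial. They can therefore attend follow-up and have the result deleted.
- The insulin secretion and resistance biomarkers are listed at weeks 104 and 208 and, in the meal-test sub-study, at follow-up. On those times, a patient rescued between weeks 104 and 208 would have the week-104 value scored as the off-drug value at week 212, 108 weeks later.
- For blood pressure, 60.4% took antihypertensives at baseline (Table 4), so medication changes are a realistic trigger.
- The only analysis described that does not use LOCF is the MMRM for HbA1c, and Table 2 lists no HbA1c at follow-up. No analysis described would therefore show the problem.

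**Within an arm.** Let D be the true off-drug minus on-drug change, and f the share of patients whose follow-up value is replaced by the same on-drug value used at end of treatment. Assume D is the same in replaced and observed patients. Replaced patients contribute a change of zero, so

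reported change = (1 − f) × D.

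The article does not give f. For assumed values of 10%, 20%, 30% and 40%, the reported change is 90%, 80%, 70% and 60% of the true one. The shrinkage always runs towards no loss after stopping.

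**Between arms.** With E for empagliflozin and G for glimepiride,

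reported contrast = (1 − f_E) × D_E − (1 − f_G) × D_G, so bias = f_G × D_G − f_E × D_E.

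Illustrations in arbitrary units (all inputs assumed):

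| D_E | D_G | f_E | f_G | True contrast | Under LOCF | Bias |
|---|---|---|---|---|---|---|
| 1 | 0 | 20% | 20% | 1.0 | 0.8 | −0.2 |
| 1 | 0.5 | 20% | 20% | 0.5 | 0.4 | −0.1 |
| 1 | 0.5 | 20% | 40% | 0.5 | 0.5 | 0 |
| 1 | 1 | 10% | 30% | 0 | +0.2 | +0.2 |
| 1 | 1 | 30% | 10% | 0 | −0.2 | −0.2 |

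With an equal share f in both arms, the bias in the off-drug difference is f × (on-drug difference − off-drug difference), a pull towards the on-drug difference. With unequal shares the sign can be negative, zero or positive.

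**The case against.** The strongest reply is that nothing in the article says outright that an on-drug value is carried past the last dose. The article condenses a fuller protocol, and a full analysis plan may stop LOCF at the end of treatment. The surrounding text concerns weeks 52 and 104, and apart from lipids no follow-up endpoint is given a model. The Endpoints section also describes the meal-test markers as assessed in patients who undergo the test, which suggests that untested patients are not imputed.

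Part of this stands. Coverage is inferred from unqualified wording, and for the meal test the missed-visit route is less certain. The deletion route remains, because a rescued patient who takes the follow-up test still has the result set to missing. Nor is this a detail left to another document: the article states a general rule, and that rule conflicts with endpoints it lists itself.

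The replaced share should not be equated with dropout. Follow-up is timed from treatment discontinuation, so early discontinuers can supply genuine off-drug values.

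A reader might infer that the empagliflozin–glimepiride comparison is necessarily biased towards a lasting empagliflozin effect. The documents do not support that. Glimepiride values are carried forward too, replaced shares may differ by arm, and a pre-rescue value may reflect poor control, so the error in level can run the other way.

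A reader might also attach false-positive rates. If the true off-drug difference is zero, with an assumed equal share of 20–40%, SD 14 mmHg, 772 per arm and an on-drug SBP difference of 2.1–4.8 mmHg, the rates run from 9% to 77%. But the share and SD are assumed, the SBP range is the placebo-corrected one from the Background rather than a difference from glimepiride, and SBP is not the beta-cell question. These figures do not measure the defect in this trial.

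**Conclusion.** The point holds in limited form. As worded, the rule lets on-drug values stand in for values four weeks off drug. Where the same value serves at end of treatment, the within-arm change on stopping is reduced by the factor (1 − f), which undermines the beta-cell assessment announced in the Discussion. This rests on a literal reading of the rule and on similar withdrawal changes in replaced and observed patients. Between arms, a pull towards the on-drug difference follows only if the replaced shares are equal; otherwise the direction is undetermined. The size cannot be stated without rescue and follow-up missingness rates. All affected endpoints are exploratory, and those for beta-cell function at follow-up sit in a sub-study. The primary and key secondary tests at weeks 52 and 104 are untouched.

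**What to change.** Add to the analysis plan: endpoints at the four-week follow-up are analysed with values measured after the last dose only, and no on-treatment value is carried into that visit.

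Report the follow-up analysis both with and without patients rescued earlier. Neither version is clean alone: values under rescue medication are not pure off-drug values, and leaving those patients out selects on glycemic control. For SBP/DBP, state whether the antihypertensive rule applies at follow-up and, if it does, treat deleted values as missing rather than carrying them forward. State which missing-data rule governs lipids.

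The cost is a few sentences and no new data. The follow-up analyses will have fewer patients and wider intervals, and the patients observed may be a selected group, so the number contributing per arm should be reported.
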